### Qualitative assessment

A focus group study with patients prior to the commencement of the trial will be carried out to assess views on current primary health care provision in Ballymun and acceptability of a lengthened multidisciplinary consultation. Semi-structured interviews will be carried out at the end of the study with a purposive sample of family participants and with all participating primary care team members. The purpose of this is to assess views of participants towards the intervention.

### Randomisation

Families are randomised to either the intervention or control group after all baseline assessments are completed (figure 2). Following randomisation, families are informed by a letter from the principal investigator of whether their family will be in the intervention or control group.

**Figure 2 F2:**
[figure not shown]
Flowchart of study intervention process.

### The intervention

Families in the intervention group will be offered a multidisciplinary consultation with the Primary Health Care Team (PHCT) to assess their health and social needs. The multidisciplinary appointments with intervention patients will be in a phased manner to protect against major service disruption. The four GPs in the study will set aside one three hour session per fortnight each for the study. Intervention families will be presented and discussed openly at the regular Primary Health Care Team meetings in order to gain maximal input and advice. The PHCT will also decide during this meeting who will attend the consultation and arrange a time and date for it. The GP will inform the family, and confirm the time and date for the consultation with the family.

The PHCT members attending the consultation will meet 10 minutes prior to the consultation to discuss the family and appoint one member of the team to lead the consultation process. This member will make introductions, explain the process to the family and open the consultation. The consultation will follow the family's agenda. All areas of health and social functioning will be explored. An appropriate management plan will be made during the consultation and agreed with the family. This will also establish the need for further lengthened consultations with members of the primary care team. A written summary of the consultation should be made for research follow up purposes. Minimum detail should include date and duration of the consultation, team members present in the consultation, and the management plan or follow up agreed from the consultation.

### Quality assurance

The research team will provide assistance to the researcher in the baseline interviews and questionnaire administration to ensure quality of data collection. All general practitioners and primary care team members attended training sessions for the multidisciplinary lengthened consultation, including role plays with simulated patients. Regular feedback on the sessions will occur at primary care team meetings attended by one of the principal investigators ([name]). All primary care members involved in the study will be asked to participate in a semi-structured interview at the conclusion of the study to understand factors influencing variation in implementation of the intervention.

### Sample size calculations

The primary outcome (HADS) is not normally distributed in the population and it is therefore not possible to do a normal sample size calculation as it is not characterised parametrically. The sample size calculation is therefore based on the Mann Whitney statistic. If the variable was normally distributed two groups of 46 families at 90% power and a significance level of 5% would be able to detect a situation in which the chances of performing better in the intervention group rather than the control group would be 75%. A total of 92 families will be required to detect this difference.

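### The stated sample size, power and 75% effect do not agree: on a Mann-Whitney basis, 46 per group at 90% power corresponds to a probability of doing better of about 0.69–0.70

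*Protocol article*

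**What the plan says.** In the Protocol article, Sample size calculations, the HADS is described as non-normal, and a normal calculation is therefore ruled out. The text goes on: "The sample size calculation is therefore based on the Mann Whitney statistic". The next sentence makes the figure conditional on the assumption just rejected: "If the variable was normally distributed two groups of 46 families at 90% power and a significance level of 5% would be able to detect". The effect to be found is then described in these terms: "the chances of performing better in the intervention group rather than the control group would be 75" per cent. The paragraph closes: "A total of 92 families will be required to detect this difference".

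The section gives no HADS difference, standard deviation, sidedness or formula. The planned analysis (Data collection, monitoring and analysis) is ordinal logistic regression adjusted for baseline.

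**The concern.** The paragraph fixes all the quantities that define a Mann-Whitney sample size: group size, power, significance level and the chance of doing better. Any three determine the fourth, so the statement can be checked, and it does not hold. The paragraph also contradicts itself on method, because it rejects normality and then relies on it.

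This is the only sample-size justification for the primary outcome, and the 75% is the only target effect given. A reader would conclude that 92 families give 90% power only for a large effect. In fact they give about that power for a clearly smaller one, so a null result would be judged against the wrong target.

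**Working it through.** **Inputs from Sample size calculations:** Mann-Whitney basis; 46 per group, N = 92, equal allocation; power 90%; significance level 5%; P(intervention better than control) = 0.75. **Assumption:** two-sided test, so (1.960 + 1.282)² = 10.507.

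**1. Attempt to reproduce 46 with Noether's Mann-Whitney formula**

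N = 10.507 / [12 × 0.5 × 0.5 × (P − 0.5)²]

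- At P = 0.75: N = 10.507 / (3 × 0.0625) = 56.04, about 28 per group. The printed 46 is not reproduced.
- A one-sided test widens the gap: 22.8 per group.

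**2. The same under a normal shift, as the text's condition suggests**

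P = Φ(d/√2), so P = 0.75 needs d = √2 × 0.6745 = 0.954.

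- Two-means formula: 2 × 10.507 / 0.954² = 23.1, so 24 per group. Dividing 24 by the Mann-Whitney efficiency of 0.955 gives about 25.
- Simulated Mann-Whitney power (20,000 runs): 0.89 at 25 per group, 0.91 at 26.

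The proportional-odds formula, which is closer to the planned analysis, has an odds ratio of about 5.1 at P = 0.75 and gives about 24 per group.

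**3. What 46 per group delivers for P = 0.75**

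- Noether: Φ(√276 × 0.25 − 1.960) = Φ(2.19) = 0.986, where 276 = 3 × 92.
- Simulated, normal shift: 0.993.

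**4. The effect that matches 46 per group at 90% power**

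- Noether: P = 0.5 + √(10.507 / 276) = 0.695.
- Simulated, normal shift: power is 0.90 at P = 0.69.

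| Reading of the 75% | 46 per group gives | 90% power needs |
|---|---|---|
| P(better) = 0.75, Noether | 98.6% power | about 28 per group |
| P(better) = 0.75, normal shift, simulated | 99.3% power | about 26 per group |
| 75% beat the average control, normal shift, simulated | 87–88% power | see step 5 |

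**5. A possible source of 46**

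The ordinary two-means formula with d = 0.6745 gives 2 × 10.507 / 0.6745² = 46.19, with power 0.899 at 46. At that d, 75% is Φ(d), the chance of beating the average control. The chance of beating a randomly chosen control is Φ(0.6745/√2) = 0.683. Simulated Mann-Whitney power at 46 per group is then 0.871 and 0.878 in two runs. The Mann-Whitney requirement would be about 48 per group (46.19 / 0.955) or 52 (Noether).

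**The case against.** **The wording is loose.** The text does not define the 75% as a random-pair probability. Read as the chance of beating the average control, and under the text's own normality condition, 46 per group and 90% do fit a two-means calculation (0.899). That is fair, and it is why the effect measure has to be defined. It does not rescue the statement, because the paragraph claims a Mann-Whitney basis and Mann-Whitney power on that reading is about 87–88%. The random-pair reading is also the natural one for that statistic.

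**The origin of 46.** A reader might infer that no Mann-Whitney calculation was done and that a factor of √2 was dropped. The document does not support this as fact, because it shows no working. The two-means route gives 46.19, which would conventionally be rounded up to 47, and it is not the only route to a number near 46:

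- One-sided Noether at P = 0.75 gives a *total* of 2 × 22.84 = 45.7, which could have been taken as a group size.
- A crude variance bound of 0.25/n gives 10.507 × 0.25 / 0.0625 = 42.0 per group, and a 1/(2n) continuity correction takes that to 45.9.

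The two-means route is probable, not proven. The inconsistency does not depend on it.

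**An unstated allowance for losses.** Going from 28 to 46 would imply 1 − 28/46 = 39% loss. The text mentions none and ties the 92 families directly to the effect. A condensed article need not print an attrition allowance, and its absence is no part of this point.

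**Consequence.** A reader might infer that the trial is too small. It is not, for a true 75% effect: the error runs the safe way. That argues for treating this as a correction of a stated figure, not as a design fault.

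**Conclusion.** The concern holds as an internal inconsistency. With P(better) as the effect measure and a two-sided 5% test, the stated 75% at 90% power needs about 26–28 per group, so 46 is about 1.6 to 1.8 times that (46/28 to 46/26). Forty-six per group gives about 99% power for 75%, and 90% power for about 0.69 (normal shift) to 0.70 (Noether). In standardised terms, the statement implies 90% power only at d = 0.95. The true figure is about d = 0.70 (√2 × 0.496 at P = 0.69).

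If the 75% means beating the average control, the shortfall is 2–3 percentage points of power. The normality contradiction stands on either reading.

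The results rest on the two-sided assumption and on an unadjusted Mann-Whitney comparison. They do not describe the power of the planned baseline-adjusted ordinal regression.

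**What to change.** Keep 92 families. Define the effect measure, and state the sidedness and the formula. Then use whichever statement matches the intended effect:

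- *If the random-pair probability is meant:* two groups of 46 give 90% power (two-sided 5%, Mann-Whitney, Noether formula) to detect a probability of superiority of about 0.70 (about 0.69 under a normal shift); power for 0.75 is about 99%.
- *If beating the average control is meant:* say so, and state that under a normal shift this is a probability of superiority of 0.68, for which Mann-Whitney power with 46 per group is about 87–88% (two-sided 5%).

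Remove the contradiction between ruling out a normal calculation and making the figure conditional on normality. Where a normal-shift figure is quoted, label it as such. If the test was meant to be one-sided, the figures must be recomputed on that basis. It would also help to say that the calculation refers to an unadjusted comparison, while the analysis adjusts for baseline.

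The cost is a few sentences of text. Enrolment does not change.

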### Data collection, monitoring and analysis

Descriptive statistics will be used to summarise patient factors for the two study groups and to compare baseline variables between control and intervention group. Outcomes between study groups will be compared to assess the effect of the intervention. Primary and secondary outcome measures at 6 months and 12 months time frames will be compared between intervention and control groups adjusting for baseline values using an ordinal logistic regression model.

### Trial organization and management

The study has received ethics approval from the Research Ethics Committee of the Royal College of Surgeons in Ireland (Ref REC2004/115). No significant risks to participants are anticipated. As the study is unblinded and low risk a data monitoring committee is unnecessary.

## Discussion

There has been little development of the general practice consultation over the years, and many aspects of the present consultation do not serve communities with multiple health and social problems well. A major strength of this study is that it provides both a new model of the consultation and the opportunity to evaluate it in a randomized controlled trial. This opportunity presents infrequently as many service developments are implemented before adequate evaluation. The study also sets out to recruit a population that is often excluded in other studies. As such, it may contribute towards a reduction in health inequity. The embedded nature of this study in general practices in a highly deprived area ensures generalisability to other deprived communities, but more particularly it promises relevance to primary care.
